### Clinician Eligibility and Recruitment

Nurse case managers (CMs), home care nurses, physicians, advanced practice providers, and administrators who are actively involved in supervisory roles or in referring to THRIVE will be invited to provide feedback on the appropriateness, accessibility, feasibility, and workload involved in referring to the THRIVE clinical pathway. During the consenting process, the research coordinator will obtain preferences for the best communication method to schedule the interview (eg, email or telephone call). A total of 22 interviews and surveys are planned. Participants who complete both the surveys and interviews will receive a US $90 gift card by mail.

### Ethical Considerations

This study was approved by the University of Pennsylvania’s Institutional Review Board (IRB #4 approved this protocol #852910 on March 10, 2023). The study will be conducted according to the Declaration of Helsinki and national regulations. Study participation is voluntary, and written consent will be obtained prior to clinician interviews. Our IRB approval includes a HIPAA (Health Insurance Portability and Accountability Act) waiver of informed consent for THRIVE participants’ clinical data. All study data collected will be deidentified, pseudonyms will be used, and data will only be accessible to the research team and stored on password-protected computers. Clinicians will be compensated US $90 by gift card for interview participation. Individual participants will not be identifiable in any published material.

### Data Collection and Management

#### THRIVE Participants and Usual Care Group

Characteristics of THRIVE participants captured in weekly case conferences (eg, home care services, social determinants of health identified and met, and community-based services) will be stored on a Research Electronic Data Capture (REDCap; developed by Vanderbilt University) database. Data will be derived from the patient electronic health record (EHR) and hospital billing system to compare the postdischarge outcomes of participants receiving THRIVE compared to those who do not. These data will be deidentified, and a HIPAA waiver of informed consent was obtained by the University of Pennsylvania’s IRB. Data will be stored on a secure password-protected data server, and access will be provided to the study statisticians ([name]), who will be blinded to the assignment of the intervention. All aspects of study design, database integrity, and study conduct will be overseen by our data and evaluation core team, which includes doctorly prepared health service researchers and statisticians.

#### Clinicians and Administrators

Case managers at PAH will be recruited and enrolled in the study per the stepped wedge design. At 8 weeks and 18 months, we will survey clinicians via Qualtrics (Qualtrics) and convene one-on-one interviews (or focus groups depending on clinician availability). Interviews will be conducted in the setting of the clinician’s choice, either in a conference room in the hospital or via Zoom (Zoom Video Communications). During interviews, clinicians and administrators will be asked for permission to audio record the interview. If the participant agrees, all conversations from that point forward will be recorded. If the clinician or administrator consents to the interview but does not agree to recording, to retain the participant, the interviewer will take detailed notes during the conversation instead of recording. Interview documents are labeled with a unique identification number stored separately for identifying information about the participant. The study timeline is outlined in a SPIRIT diagram (Figure 2).

**Figure 2 figure2:**
[figure not shown]
SPIRIT (Standard Protocol Items: Recommendations for Interventional Trials) diagram—THRIVE schedule of evaluations. ED: emergency department; PCP: primary care provider.

### Sample Size

We anticipate a sample size of 534 inclusive of THRIVE referrals and the comparison group (derived from the EHR). Based on a power analysis, a sample size of 472 (236 THRIVE participants and 236 comparisons) for the outcome of readmissions, or a sample of 534 (267 THRIVE participants and 267 comparisons) for the outcome of ED visits, will yield 80% power to detect significance at the .05 level. We will target a sample size of 534 to ensure adequate power for both outcomes. We anticipate consenting 22 clinicians and administrators to complete surveys and interviews to provide data for implementation outcomes.

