#### Randomization

Groups of case managers (4 in the first group, 4 in the second, and 5 in the third) were randomly assigned by the study methodologist to each sequence using a random number generator. A stepped wedge design—that is, a 1-time crossover design—was used for THRIVE (Table 2).

Specifically, following a baseline data collection period, 4 case managers will be randomized to receive training on the THRIVE clinical pathway. Following training, they begin referring to the THRIVE clinical pathway. At 8-week intervals, the remaining case managers will be trained in the THRIVE intervention and will be able to begin submitting referrals. Since case managers from the sequences work within the same space, the ability to conceal allocation was limited; however, all case managers were made aware of their upcoming ability to refer to the THRIVE clinical pathway.

**Table 2 table2:** Study design for the type 1 hybrid effectiveness-implementation stepped wedge cluster randomized controlled trial of the THRIVE clinical pathway.

Cluster	Baseline (3 months)	Enrollment period 1 (8 weeks)	Enrollment period 2 (8 weeks)	Enrollment period 3 (8 weeks)	Follow-up (18 months)
Sequence 1 (4 case managers)		✓	✓	✓	✓
Sequence 2 (4 case managers)			✓	✓	✓
Sequence 3 (5 case managers)				✓	✓

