##### Analysis

We will develop monthly reports to monitor the referral patterns to the THRIVE clinical pathway. The target estimate and effect measure is the time-adjusted difference in participant outcomes [53,54]. The analysis of use outcomes (eg, 30-day readmissions and ED use) will use a mixed effects negative binomial regression model with random effects for the medical team and fixed effects for time to account for the stepped wedge cluster randomized design. Sensitivity analyses may be performed using logistic regression for health service use based on the distribution of the data. We will also examine the stability of effect estimates using generalized estimation equations with small sample adjustment, given the study design [55].

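### The 80% power is stated for two equal patient groups with no visible allowance for the stepped wedge; if it is a plain 1:1 calculation, 534 patients give about 35–47% for the same effect

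*Protocol article*

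**What the plan says.** The Sample Size section gives "a sample size of 472 (236 THRIVE participants and 236 comparisons) for the outcome of readmissions" and "a sample of 534 (267 THRIVE participants and 267 comparisons) for the outcome of ED visits, will yield 80% power", with "80% power to detect significance at the .05 level". It concludes: "We will target a sample size of 534 to ensure adequate power for both outcomes". It states no control risk, effect, sidedness, ICC or formula.

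The Randomization section describes a different structure. "Groups of case managers (4 in the first group, 4 in the second, and 5 in the third) were randomly assigned", and "At 8-week intervals, the remaining case managers will be trained in the THRIVE intervention". Table 2 shows a 3-month baseline with nobody exposed, three 8-week enrolment periods with one sequence crossing over in each, and a follow-up column with everybody exposed.

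The Aim 1 Analysis section makes a time-adjusted difference the target. It specifies a mixed negative binomial model with "random effects for the medical team and fixed effects for time to account for the stepped wedge cluster randomized design".

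**The concern.** Once the model contains time effects, most of the contrast between exposed and unexposed patients is absorbed by the calendar. At baseline every case manager is unexposed, and from period 3 on every one is exposed. Exposed and unexposed case managers coexist only in periods 1 and 2, which is 16 weeks. A calculation that treats 267 and 267 as two concurrent, independent groups takes no account of this.

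Readmission and ED use make up most of Hypothesis 1, and they are the only outcomes for which power is quoted. If real power is well below 80%, a null result could be read as evidence against THRIVE from an adequately powered trial.

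**Working it through.** **1. Can the stated figures be reproduced?** Not from the document, because no effect is given. The pooled two-proportion formula, two-sided 0.05 and 80% power, was applied to the pilot's 50% reduction and the background rates in the Introduction:
- 24% to 12% needs 160 per group.
- 20% to 10% needs 199 per group.
- 34% to 17% needs about 103 per group.

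None gives 236 or 267. Solving backwards, a halving gives 236 from a control risk of about 17.3% and 267 from about 15.5%. Neither risk is in the document, so this shows only that a plain 1:1 calculation is a possible source.

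**2. Effect implied by a plain 267 + 267 test.** In standard deviation units, d = (1.960 + 0.842) × √(2/267) = 0.242. The variance of that estimate is 2/267 = 0.00749.

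**3. Same effect, actual design, ICC 0.** Inputs from the article are 13 case managers (4/4/5), a baseline of 3 months (taken as 13 weeks), and three 8-week periods. Assumptions are 534 patients spread evenly over case managers and weeks, a categorical period effect, and comparisons only from unexposed case managers. With period effects and no clustering,

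variance = 1 / Σ nₜ πₜ(1 − πₜ),

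where nₜ is the number of patients in period t and πₜ the exposed share. Baseline (π = 0) and period 3 (π = 1) contribute nothing.
- nₜ for an 8-week period = 534 × 8/37 = 115.5.
- Period 1: 115.5 × (4/13)(9/13) = 24.6.
- Period 2: 115.5 × (8/13)(5/13) = 27.3.
- Variance = 1/51.9 = 0.0193, which is 2.57 times 0.00749. The standard error is 0.139.
- Power = Φ(0.242/0.139 − 1.96) = about 42%.

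With four equal periods, nₜ = 133.5, the variance is 1/60.0 = 0.0167 (ratio 2.22), and power is about 47%.

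The same ratios apply to 472 patients and the effect that 236 + 236 would detect.

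**4. With clustering.** Generalised least squares on case-manager-by-period means, with a random case-manager effect. The ICC values are assumed.

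| ICC | Variance ratio, 13/8/8/8 weeks | Power | Power, equal periods |
|---|---|---|---|
| 0 | 2.57 | 42% | 47% |
| 0.01 | 2.82 | 38% | 43% |
| 0.05 | 3.15 | 35% | 38% |
| 0.10 | 3.17 | 35% | 37–38% |

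Reaching 80% for this effect would take 2.22 × 534 to 3.17 × 534, or about 1,190 to 1,690 patients. A t reference with 11 degrees of freedom lowers the power range to about 30–40%.

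**5. If post-rollout patients share the 534.** Baseline plus rollout is 37 weeks. Data collection from March 2023 to July 2024 leaves roughly 36 more weeks, all exposed. At ICC 0, nₜ in periods 1 and 2 falls to 534 × 8/73 = 58.5, and the variance is 1/(58.5 × 76/169) = 0.0380 (ratio 5.07). Power is about 24%. Across ICC 0–0.10 it is about 22–24%.

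**The case against.** **Origin of the figures.** The strongest reply is that the sentence cannot be shown false. Some effect gives 80% power at 534 under any design, no effect is stated, and the derivation may sit in a fuller document. Halving the 34% ED rate from the Introduction even gives about 80% under the stepped wedge at ICC 0. That rate is annual, whereas the outcome is 30-day, and the parallel check for readmissions fails: 24% to 12% with 472 patients gives about 49–56% at ICC 0–0.05 with 13/8/8/8 weeks. A reader might infer that the power is certainly from an individually randomised calculation. The equal split and the missing design terms point that way, but the document does not say so.

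**Model.** The planned model is negative binomial with a medical-team effect. The check uses a common-variance approximation with case managers as clusters. This affects the lower end of the range. It leaves the ICC 0 result, where no cluster effect enters, largely untouched.

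**Comparison group.** The article does not clearly exclude concurrent non-referred patients. Counting them gives about 41–54% during rollout and 43–70% with post-rollout patients, so post-rollout patients can then add power. That remains below 80% and is no longer the randomised contrast. The Current Usual Care section places control patients in the control phases.

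**Post-rollout period.** The 22–24% needs categorical period effects; a linear time trend gives about 37%. A reader might also infer a still lower figure by adding Table 2's 18-month follow-up column to the rollout. The article gives 18 months for all data collection, ending in July 2024, so that scenario is not supported.

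**Status of the outcomes.** Outcomes and Measures calls readmission and ED use secondary, while the Design overview lists them as primary. Under either label, they are the outcomes for which adequate power is claimed.

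**Conclusion.** The concern stands in conditional form. The published power statement shows no allowance for time effects or clustering, and the design and analysis sections require both. If the counts are a plain 1:1 calculation, power for the same effect is about 42–47% at ICC 0 and about 35–38% at ICC 0.05–0.10. It is about 22–24% if 36 all-exposed weeks share the 534 under the assumptions in step 5. The loss is already there at ICC 0, so it does not depend on the assumed ICC or on which unit is the cluster. It does rest on even accrual, categorical period effects and a comparator confined to control phases. That the calculation was 1:1 is inferred and should not be reported as fact.

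**What to change.** State the assumed control risks and effect for both outcomes. Replace the power sentence with power, or the minimum detectable difference, for the actual design: 13 case managers in sequences of 4/4/5, baseline plus three 8-week periods, period effects, and a range of ICCs. Say whether post-rollout patients count toward the 534.

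Do not cap the EHR comparison group at 267; use every eligible control-phase discharge. Tripling the control cells at ICC 0 gives, from treated and control counts in each period:
- Period 1: 35.5 × 239.8 / 275.3 = 30.9.
- Period 2: 71.1 × 133.2 / 204.3 = 46.3.
- Variance = 1/77.3 = 0.0129, against 0.0193.

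That is a cut of about one third, and 31–37% across the ICCs tried. Power at ICC 0 rises from about 42% to Φ(0.242/0.114 − 1.96) = about 57%, so the larger extract helps but does not restore 80% on its own.

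The cost is one rewritten paragraph, a less favourable stated figure and a larger EHR extract. The comparison data already come from the EHR under the consent waiver, so no new recruitment is needed.

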### The THRIVE Intervention

#### Current Usual Care

To provide evidence of the effectiveness and implementation of THRIVE, we will compare individuals receiving THRIVE services to patients receiving usual care. The current usual care will serve as the control condition that patients will receive during the control phases of the design. Usual care may include discharge care planning that reflects the patient’s medical needs, which may or may not include referrals to home care, skilled nursing or rehabilitation facilities, and other outpatient services.

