### THRIVE Eligibility Criteria

Individuals eligible for a THRIVE referral include (1) being Medicaid insured, dually enrolled in Medicaid and Medicare, or Medicaid eligible; (2) residing in Philadelphia; (3) having experienced a hospitalization at the study hospital for more than 24 hours with a planned discharge to home; (4) agreeing to home care at partner home care settings; and (5) being aged 18 years or older. If home care services are declined at any time following discharge, THRIVE services are also discontinued. If palliative or hospice services are ordered following discharge, THRIVE services will not be offered.

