### Evaluation

#### Aim 1

Aim 1 is to examine referral patterns, 30-day readmission, and 30-day ED use patterns for participants who receive THRIVE support services compared to those receiving usual care.

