	**Proctor implementation outcomes**										
		Acceptability^i^ Appropriateness^j^ Feasibility^k^	Mixed methods approach to determine the Proctor implementation outcomes					Survey and interviews with clinicians and administrators			8-week postintervention from the start of each sequence and at the study end
		Fidelity^l^	Retrospective chart review					Standardized THRIVE checklist			Monthly

^a^ED: emergency department.

^b^Proportion of THRIVE referrals of those who are THRIVE eligible.

^c^Proportion of THRIVE participants experiencing the outcome within 30 days of discharge compared to usual care group.

^d^Organizational commitment to addressing disparities.

^e^Relative advantage of THRIVE to patients, degree of fit with existing practice, competing demands, and bias.

^f^Structures outside of the hospital that affect patient care.

^g^Organizational values, culture embedding, and championing adaption.

^h^Organizational priorities and goals and readiness for change and culture or climate.

^i^How fair or reasonable THRIVE is deemed.

^j^To what extent THRIVE seems suitable.

^k^The practicality and ease of delivering THRIVE.

^l^Fidelity to THRIVE’s core components.

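### Readmission, ED use and care visits are compared by who received THRIVE, not by the case manager's randomised condition, so selection into referral and home care enters the contrast

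*Protocol article*

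**What the plan says.** **What is randomised.** Under Randomization: "Groups of case managers (4 in the first group, 4 in the second, and 5 in the third) were randomly assigned" to the three sequences of the rollout.

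**What is compared.** For the post-discharge outcomes, several sections define the contrast by receipt of the service:
- Evaluation, Aim 1 (and, in the same terms, Aims and Hypotheses): "participants who receive THRIVE support services compared to those receiving usual care".
- Data Collection and Management, THRIVE Participants and Usual Care Group: the extracted data will "compare the postdischarge outcomes of participants receiving THRIVE compared to those who do not".
- Current Usual Care: "we will compare individuals receiving THRIVE services to patients receiving usual care".
- Table 3, footnote c, which covers readmissions, ED visits, and primary and specialty care visits: "Proportion of THRIVE participants experiencing the outcome within 30 days of discharge compared to usual care group".

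The Sample Size section also counts THRIVE participants against comparisons, 236 and 236 for readmissions and 267 and 267 for ED visits.

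**Who enters each group.** THRIVE Eligibility Criteria requires "agreeing to home care at partner home care settings", and adds: "If home care services are declined at any time following discharge, THRIVE services are also discontinued". Usual care is described as discharge planning "which may or may not include referrals to home care, skilled nursing or rehabilitation facilities".

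**Index event.** Under Outcomes and Measures (Aim 1), THRIVE patients are followed from the hospitalization that led to referral. Usual-care patients are followed from their first index hospitalization of the calendar year.

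**The concern.** A stepped wedge trial protects against confounding only when each patient is analysed under the condition their cluster was in at the time. Referral and agreement to home care both happen after the case manager's condition has been set, and both can be related to readmission risk. A group defined by having passed those two steps is no longer the group that randomisation made comparable.

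Under the stated contrast, an eligible patient of a trained case manager who is not referred, or who refuses home care, is not a THRIVE participant. Implementation Strategies expects such patients, since a dashboard will record who was eligible but not referred. The article nowhere places them in their case manager's condition. Table 2 sharpens this: once the third sequence starts, 16 weeks after the first, an eligible patient of these 13 case managers can be in usual care only by not being referred or not agreeing. The calendar-year index rule does not confine comparators to earlier dates.

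At stake is whether the effectiveness result can be read as randomised evidence. The Introduction presents this trial as a more rigorous evaluation than the nonrandomised pilot.

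**Working it through.** **1. The plan's own figures.** The article gives 472 (readmissions) and 534 (ED visits) for 80% power at .05, but no event rates, effect size or sidedness, so they can be neither confirmed nor refuted. To have a working scale, I take as control rates the two figures in Background: 24% readmission and 34% ED use. The article does not say these were the power inputs, and the 34% is annual. With a two-sided test of two proportions and no continuity correction:
- 236 per arm detects 24% against 13.9%, a 10.1-point difference.
- 267 per arm detects 34% against 23.05%, a 10.95-point difference.

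Other pairs fit as well, for example 19% against 10% (readmissions) and 26% against 16% (ED visits).

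**2. Selection alone, with no true effect.** Let *a* be the share of eligible patients who accept and *k* the decliners' risk relative to accepters. Both are assumptions, and no covariate adjustment is made. Accepters against all eligible patients give

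RR = 1 / [a + (1 − a)k]

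- a = 0.5, k = 1.5: 1/(0.5 + 0.75) = 0.80
- a = 0.5, k = 2: 1/(0.5 + 1.0) = 0.67
- a = 0.5, k = 0.7: 1/(0.5 + 0.35) = 1.18
- a = 0.3, k = 2: 1/(0.3 + 1.4) = 0.59
- a = 0.3, k = 0.7: 1/(0.3 + 0.49) = 1.27

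The last two are the extremes for a from 0.3 to 0.7 and k from 0.7 to 2.0.

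**3. Chance of a significant result favouring THRIVE when there is no effect.** With overall risk p and accepter risk pₐ, the chance is Φ[(p − pₐ − 1.96·SE₀)/SE₁], where SE₀ is pooled and SE₁ unpooled. Assume a = 0.5 and accepters at 0.7 times decliners' risk, so that pₐ/p = 0.7/0.85 = 0.82.
- Readmission, 236 per arm: p = 0.24, pₐ = 0.198; about 20%.
- ED visits, 267 per arm: p = 0.34, pₐ = 0.280; about 32%.

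The nominal figure is 2.5%. If accepters are the sicker patients, the bias works against THRIVE instead.

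**4. Power when all eligible patients are analysed.** If a share *u* receives THRIVE and the rest are unaffected, the difference becomes u times the difference in step 1. Per arm,

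n = [1.96√(2p̄(1 − p̄)) + 0.84√(p₀(1 − p₀) + p₁(1 − p₁))]² / (p₀ − p₁)²

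At u = 0.5, readmission: p₁ = 0.24 − 0.5 × 0.101 = 0.1895 and n = 1037. ED visits: p₁ = 0.34 − 0.5 × 0.1095 = 0.28525 and n = 1125.

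| Uptake u | Readmission: total N | Power at 236 per arm | ED: total N | Power at 267 per arm |
|---|---|---|---|---|
| 1.0 | 472 | 80% | 532 | 80% |
| 0.8 | 766 | 59% | 852 | 60% |
| 0.6 | 1416 | 37% | 1546 | 38% |
| 0.5 | 2074 | 27% | 2250 | 28% |

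No clustering is included, so these totals are lower bounds. Uptake is an assumption.

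**The case against.** The case for the plan has five parts.

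- **Control phases and time effects.** Current Usual Care also calls usual care the condition patients receive in the control phases, and the Aim 1 Analysis section fits fixed effects for time because of the stepped wedge. This shows awareness of the design and makes the definition less than uniform. But neither sentence says patients are analysed by their case manager's condition, and the random effect named is for the medical team. Even if every comparator came from a control phase, accepters would still be compared with accepters and decliners together. Time effects adjust between periods, not for selection within one.
- **Covariates.** Demographics, comorbidities, unit and discharging team will be collected. Adjustment may reduce the bias, and the risk ratios shown here are unadjusted. It does not restore a randomised comparison.
- **The referral rate.** Outcomes and Measures compares it with baseline and with case managers not yet crossed over, and Table 3, footnote b, uses eligible patients as denominator. This stands: that outcome is sound on this point.
- **Incomplete definitions.** The article does not fully define the comparators. It makes the all-payor comparison secondary, which suggests a narrower main group. It says services stop when home care is declined, not that the patient leaves the analysis. Both points stand as limits on what can be claimed.
- **Condensed format.** Detail may sit in a fuller document. But the contrast is stated repeatedly, so further detail would have to replace it, not merely add to it.

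**Conclusion.** The point holds for 30-day readmission, ED use, and primary and specialty care visits. As written, their contrast is by receipt of THRIVE, with referral and home-care agreement required on one side, not stated for the other, and different index rules. Under the assumptions shown, selection alone moves a null risk ratio to 0.80 or to 1.18. Neither size nor direction can be determined from the article.

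A reader might infer more than the document supports:
- **That the trial discards its randomisation.** It does not for the referral rate, which Outcomes and Measures names as the primary outcome. (Design and Randomization lists readmission and ED use as primary too, a separate inconsistency.)
- **That comparators are wholly unselected, or that patients who stop are dropped.** The article settles neither.
- **That the bias favours THRIVE, or equals the effect sought.** The sign is unknown and no target effect is stated. The only effect given is the pilot's 50% decrease, which the range 0.59 to 1.27 does not reach.
- **That the pilot's selection is repeated.** The article does not describe how the pilot's groups were formed.

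**What to change.** For the post-discharge outcomes, make the main analysis intention-to-treat:
- Include every discharge meeting eligibility criteria 1, 2, 3 and 5 (payer, Philadelphia residence, stay over 24 hours with planned discharge home, adult age), found by the same health-record rule in both conditions.
- Use the same index-hospitalization rule in both conditions.
- Classify each discharge by whether the patient's case manager had crossed over at discharge, regardless of referral, acceptance or discontinuation.
- Keep the receipt-based contrast as secondary, for example as a complier-average effect with case-manager condition as instrument. This assumes that training affects outcomes only through THRIVE.
- Bring Aim 1, the data-collection text, Current Usual Care and Table 3, footnote c, into line.

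**Cost.** The data burden is small: the record-based flag and the eligibility dashboard already identify eligible patients, so the extract needs a case-manager identifier and discharge date. The real cost is power. Uptake dilutes the effect, so the 80% in Sample Size no longer holds at 534 if uptake is incomplete and the calculation assumed the effect in recipients. Restate it for the expected number of eligible discharges, the expected uptake and the clustering. Eligible discharges may well exceed 534, which would recover part of the loss, but the article gives no count from which to say how much.
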